### Statistical analysis

All analyses will be conducted according to the intention-to-treat principle. All participants who have been randomized will be included in the analyses examining the differential effects of the interventions. Missing data will be imputed using regression imputation. To examine differences between the conditions, we will use multiple regression analyses with symptoms of depression and anxiety as dependent variables and d the treatment dummy as predictor. By using multiple regression analyses, we can correct for possible confounders. All analyses will be conducted using SPSS for Windows, version 15.

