Although the efficacy of internet-based self-help has been demonstrated sufficiently, it is not clear how these interventions should be offered to the population who can benefit from it. A major issue, for example, is whether it is better to offer the intervention with the support of a coach or if automated programs could work. In case support is necessary, it is not clear which level of support is needed. One of the advantages of a system without a coach is the ease and low costs of implementation, as it does not require a complex and costly structure of professionals. Furthermore, there is virtually no limit as to how many clients can enter the program, since additional clients will not imply additional therapist time [4]. On the other hand, a system organization, in which participants have to be assigned to coaches, will account for high costs and is more difficult to organize, since the coaches have to be trained, have to have sufficient time and have to be paid. There will also be limits on the amount of participants entering the program. However, legal and ethical issues of unguided programs (e.g., disappointment if the treatment fails, and the question of responsibility), the necessary risks of failing to identify cases for whom pure self-help is not enough, and the inability to monitor patients and adjust their treatment when necessary (e.g., in crisis situations) are arguments against unguided programs.

There is evidence that in interventions without a coach, compared to interventions with a coach, the drop-out rate is considerably higher [12]. Moreover, although interventions without a coach can be effective in reducing depressive and anxiety symptoms, they are associated with much smaller effect sizes than interventions in which the user had regular contact with a coach [12]. How large the differences in effectiveness are between interventions with and those without a coach has not been sufficiently studied. Moreover, it has not been examined whether there are differences in drop-out rate and costs between interventions with and without support, and in particular different levels of support. The aim of this study is to examine whether an internet-based self-help intervention with a coach is more effective than the same intervention without a coach in terms of clinical outcomes, drop-out and economic costs. Furthermore, this study examines which level of support by a coach is more effective compared to other levels of support.

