### Sample size

The effects of the intervention on symptoms of depression and anxiety are the primary outcome measures and these are used as starting point for the power calculations. We assume that we want to be able to show differences between interventions and the control conditions with a standardized effect size (Cohen's *d*) of 0.35 [13]. Smaller effect sizes are considered to be not relevant from a clinical point of view. Assuming an alpha of 0.05 and a statistical power (1-Beta) of 0.80 in a one-tailed test, we need 100 respondents in each of the conditions. Overall, we need to recruit 500 respondents in total.

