This study has several limitations. First, there could be selective drop-out in the non-internet-intervention groups (control condition 4: support only; control condition 5: only information). In the analysis, we will examine whether this happened. Furthermore, we will make use of intention-to-treat analysis, in which missing values are estimated with different techniques (e.g., multiple regression, multiple imputation). Second, the control group receives information only, which can be effective in reducing symptoms of depression and anxiety, although effect sizes are small [11]. Third, psychometric properties of some of the questionnaires used in this study are not yet tested for online use, although this can be different from its paper-pencil versions [55]. One of the reasons is that people sometimes disclose more sensitive information in computer-based compared to face-to-face interviews [56]. A final limitation of this study concerns the sole use of self-rated instruments as outcome measures and the lack of a diagnostic interview; hence we have no knowledge whether subjects meet the criteria for a DSM-IV diagnosis of depression or anxiety. The lack of the gold standard of diagnosing makes it difficult to compare with other studies. However, since this preventive intervention is aimed to be applicable and accessible for a broad population of people from the community with clinically relevant symptoms of depression and anxiety [19], a formal diagnosis will not be necessary for participants to enter the program.

One of the strengths of this study concerns the formal evaluation of the cost effectiveness for the different levels of support given in the intervention, which has not been studied sufficiently previously [4]. Furthermore, by including the condition in which no intervention is given but only support of a coach, we will be able to examine the non-specific effects of coaching. Finally, external validity is a strong aspect of this study, since specific attention is given in the recruitment process to include patients with different ethnic backgrounds and socioeconomic groups.

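### Missing outcomes are to be filled by regression imputation and analysed as if observed; the Discussion names other techniques, and neither section says which is primary

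*Protocol article*

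**What the plan says.** The Statistical analysis section sets the analysis population first: "All participants who have been randomized will be included in the analyses examining the differential effects of the interventions". It then gives the handling of missing outcomes in one sentence: "Missing data will be imputed using regression imputation". The analysis itself is multiple regression of the depression and anxiety scores on a treatment dummy, with correction for possible confounders. Nothing is said about repeated draws, pooling or any adjustment of the standard errors for imputed values.

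The Discussion describes the same intention-to-treat analysis differently: "missing values are estimated with different techniques (e.g., multiple regression, multiple imputation"). It does not rank these techniques or call any of them primary.

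The Sample size section fixes 100 per condition, 500 in all, with no allowance for missing outcomes. No rate of missing data is given anywhere.

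**The concern.** A regression prediction put in place of a missing score is not an observation. If it is filled in once and the completed data go through ordinary regression, the software counts it as one. Two errors are possible, and the protocol does not say enough to tell which would occur:

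- If treatment arm is a predictor in the imputation model, the imputed scores repeat the arm difference already seen in the observed data, with too little scatter and a full count of participants. Standard errors are too small, intervals too narrow and p-values too low.
- If arm is not a predictor, imputed scores are the same across arms for given covariates, and the estimated difference is pulled towards zero.

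Either error would affect the comparisons of symptoms of depression and anxiety on which the trial is powered. Because the Discussion allows several techniques without ranking them, the choice could also be made after their different results have been seen.

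**Working it through.** **Inputs from the protocol.** The Sample size section gives the target difference as a "standardized effect size (Cohen's *d*) of 0.35" and sets the error rates as follows: "Assuming an alpha of 0.05 and a statistical power (1-Beta) of 0.80 in a one-tailed test". The design has five equal arms of 100. The Statistical analysis section does not state whether tests are one- or two-sided, so both are shown.

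**Assumed, because the protocol gives no value.** Share missing m from 10% to 50%, equal in both arms and completely at random; correlation of 0.5 between outcome and imputation predictor.

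**Step 1: the plan's own figure.** n per arm = 2(z₀.₉₅ + z₀.₈₀)²/d² = 2(1.645 + 0.842)²/0.35² ≈ 101. Power at 100 per arm is 0.797. The stated 100 is reproduced, for complete data and a one-tailed test (a two-sided test would need 129).

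**Step 2: arm in the imputation model, same covariates in the analysis, no random residual.** The estimate equals the complete-case estimate, so its true variance is proportional to σ²/[n(1−m)]. The reported variance uses a residual variance shrunk to about (1−m)σ² and the full n, so it is proportional to (1−m)σ²/n. The ratio of reported to true variance is (1−m)², so reported SE / true SE ≈ 1−m. The two-sided false-positive rate is 2[1−Φ(1.96(1−m))]; the one-tailed rate is 1−Φ(1.645(1−m)). At m = 0.30 these give 0.170 and 0.125.

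**Step 3: the same, with one random residual added to each prediction.** The true variance becomes proportional to 1/(1−m) + m and the reported variance to 1, so reported SE / true SE ≈ 1/√(1/(1−m)+m). At m = 0.30 the rates are 0.136 two-sided and 0.105 one-tailed.

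**Step 4: simulation under no effect** (100 per arm, 4,000 trials per setting, covariate-adjusted analysis, arm in the imputation model):

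| Missing | No residual: SE ratio | One-tailed | Two-sided | Random residual: SE ratio | One-tailed | Two-sided |
|---|---|---|---|---|---|---|
| 10% | 0.89 | 0.072 | 0.079 | 0.92 | 0.067 | 0.075 |
| 20% | 0.80 | 0.095 | 0.120 | 0.83 | 0.084 | 0.106 |
| 30% | 0.70 | 0.122 | 0.168 | 0.77 | 0.099 | 0.131 |
| 40% | 0.59 | 0.163 | 0.246 | 0.70 | 0.124 | 0.172 |
| 50% | 0.49 | 0.212 | 0.337 | 0.62 | 0.148 | 0.219 |

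The SE ratio is reported over true. Simulation and formulas agree closely. If the final analysis omits the covariate, the inflation without a residual is smaller: 0.054 to 0.168 one-tailed and 0.065 to 0.252 two-sided over the same range. As a reference, complete-case analysis of the same data gives 0.043 to 0.056, so the imputation step causes the inflation.

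**Step 5: arm left out of the imputation model.** The simulated false-positive rate is 0.042 to 0.058 at every level, so there is no inflation. But each arm's mean becomes (1−m) times its own mean plus m times a common mean, so a difference δ becomes (1−m)δ. For δ = 0.35 this is 0.35 × 0.9 = 0.315 at 10% missing, 0.35 × 0.7 = 0.245 at 30% and 0.35 × 0.5 = 0.175 at 50%. This step is algebra; the simulation was run under no effect only.

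**The case against.** The strongest reply is that the imputation sentence is short because the source is a journal article. It does not say that imputation is done once, whether a residual is added or which predictors are used, and a fuller plan may settle all three. The Discussion already names multiple imputation and can be read as adding it alongside regression imputation.

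Part of this stands. Single imputation is the plain reading of the Statistical analysis section, not its wording, and the size of the error depends on details that are not given. But the section does state a method, follows it with ordinary regression and mentions no correction. If the Discussion only adds sensitivity analyses, regression imputation remains primary. If it replaces the method, the two sections conflict.

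Two stronger readings are tempting and are not supported:

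- A reader might infer that the trial's false-positive rate will be a fixed multiple of nominal, say two to five times. No missing rate is given. With arm in the imputation model and a covariate-adjusted analysis, the multiple without a residual runs from 1.4 (0.072/0.05) to 4.2 (0.212/0.05) one-tailed and from 1.6 (0.079/0.05) to 6.7 (0.337/0.05) two-sided. With arm left out it is about 1.
- A reader might infer that the protocol expects more missing outcomes in the arms without a coach. The Background reports earlier evidence on drop-out from interventions and makes no forecast of missing questionnaires in this trial. The Discussion's own worry is selective drop-out in conditions 4 and 5, and condition 4 has a coach. Reminders for the post-test go to all five conditions.

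**Conclusion.** The concern holds in conditional form. The protocol states a missing-data method that, followed as written, treats imputed scores as observed, and it does not say whether that method or one of those in the Discussion is primary. The two possible harms differ in kind: overstated precision with arm in the imputation model, or an effect biased towards zero with arm left out. Under attenuation the test itself keeps its level. However, the Sample size section regards effects below 0.35 as clinically irrelevant, so a true effect of exactly that size would tend to be reported below the trial's own threshold.

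The figures rest on 100 per arm, an assumed 10% to 50% missing, equal and completely-at-random missingness, and an assumed correlation of 0.5, which nearly cancels when imputation and analysis use the same covariates. Selective drop-out, which the Discussion considers possible, could add bias not counted here.

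**What to change.** In the Statistical analysis section, replace the imputation sentence with one named primary method. Either of these is suitable:

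- multiple imputation with treatment arm, baseline scores, medication and outcomes at the other measurement times in the imputation model, with results pooled by Rubin's rules; or
- a likelihood-based mixed model for repeated measures fitted to the observed data.

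Table 1 schedules all four primary instruments at baseline and at three later times, so either can be supported. Keep single regression imputation as a sensitivity analysis at most, and have the Discussion name the same primary method.

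The cost is wording, some programming and possibly software other than the SPSS version named. Nothing changes for participants. Intervals become wider because they reflect the information actually collected. As a guide, complete-case power at d = 0.35, one-tailed and without covariate gain, is Φ(0.35√(100(1−m)/2) − 1.645): 0.76 at 10% missing, 0.72 at 20%, 0.66 at 30%, 0.61 at 40% and 0.54 at 50%, against 0.80 with complete data. Missing data cause that loss; the present wording could hide it.

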### Randomization

Based on three factors (depression and anxiety scores, prescribed medication for anxiety or depression), participants will be randomized after the baseline measurement. Subjects will be randomized into five groups (the three active treatment conditions and two control conditions) using block randomization with variable sizes. The allocation schedule will be made with a computerized random number generator by an independent researcher and will be unknown to the investigators.

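### The primary regression names only the treatment dummy and makes adjustment optional; it does not commit to the baseline score or the randomisation factors, all known before randomisation

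*Protocol article*

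**What the plan says.** The Statistical analysis section of the protocol article sets out multiple regression with depression and anxiety symptoms as dependent variables. Its description of the right-hand side is "the treatment dummy as predictor. By using multiple regression analyses, we can correct for possible confounders". That is all it says about the model terms. It names no covariate, and the second sentence describes what the method allows rather than what will be done.

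The Randomization section says: "Based on three factors (depression and anxiety scores, prescribed medication for anxiety or depression), participants will be randomized after the baseline measurement". Allocation to the five groups is by blocks of variable size. The section does not say which scales or cut-offs define the depression and anxiety factors.

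Table 1 lists CES-D, PHQ-9, HADS and BAI, the four primary symptom measures, at baseline and at every later assessment. Medication use is also collected as a participant characteristic.

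The Sample size section works from "a standardized effect size (Cohen's *d*) of 0.35" and continues: "Assuming an alpha of 0.05 and a statistical power (1-Beta) of 0.80 in a one-tailed test". It arrives at 100 per condition and 500 in total, and mentions no covariate.

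**The concern.** In a randomised comparison, covariates are included to gain precision and to reflect how participants were allocated. Confounding is the wrong ground, because randomisation already deals with it on average. Describing the covariates as possible confounders therefore points the analyst away from the two sets of variables that matter most here: the baseline value of the outcome and the factors that steer the allocation.

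Two things follow if the model is run as stated.

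- Variation in the outcome that the baseline score would explain stays in the residual. Every comparison is then less precise than the collected data allow.
- If allocation is balanced on factors that predict the outcome and the model ignores them, the model's standard error is larger than the true sampling variation of the treatment difference. The test rejects less often than its nominal level.

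The aim is to separate arms that share the same web programme and differ only in support. Such differences may be modest, so precision that costs nothing is worth securing in advance.

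**Working it through.** **Inputs.** From the Sample size section: d = 0.35 (SD 1 on the standardised scale), one-tailed alpha 0.05, power 0.80, 100 per condition. The correlation r between baseline and outcome is not in the document. It is assumed, over the range 0.3 to 0.7. No missing data are allowed for.

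**Step 1: reproduce the plan's figure without covariates.**

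n per arm = 2(z₀.₉₅ + z₀.₈₀)² / d² = 2(1.645 + 0.842)² / 0.35² = 100.9, that is 101.

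The plan says 100, so the figure reproduces. Power at 100 per arm is Φ(0.35·√(100/2) − 1.645) = Φ(2.475 − 1.645) = 0.797. The noncentral t distribution gives 0.794. The planned 100 is therefore an unadjusted calculation, and it delivers its stated power without covariates.

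**Step 2: adjust for the baseline score.** The residual SD becomes √(1 − r²), so the effective effect size is 0.35/√(1 − r²). The equivalent unadjusted sample size is 100/(1 − r²).

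| r (assumed) | 1 − r² | Effective d | Power, normal | Power, t | Equivalent unadjusted n per arm |
|---|---|---|---|---|---|
| 0 | 1.00 | 0.350 | 0.797 | 0.794 | 100 |
| 0.3 | 0.91 | 0.367 | 0.829 | 0.827 | 110 |
| 0.5 | 0.75 | 0.404 | 0.887 | 0.886 | 133 |
| 0.7 | 0.51 | 0.490 | 0.966 | 0.965 | 196 |

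**Step 3: direction of the error if balanced factors are ignored.** Take the extreme case of perfect balance on a factor with outcome correlation r. The true SD of the treatment difference shrinks by √(1 − r²), but the unadjusted model does not know this. The true one-sided type I error is 1 − Φ(1.645/√(1 − r²)):

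- r = 0.3: 1 − Φ(1.724) = 0.042
- r = 0.5: 1 − Φ(1.899) = 0.029

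Both lie below 0.05, so the error is conservative. In the same extreme case, unadjusted power is Φ((2.475 − 1.645)/√(1 − r²)), which is 0.808 at r = 0.3 and 0.831 at r = 0.5. Balance alone therefore recovers part of the gain. Adjustment recovers the rest, to 0.829 and 0.887. With imperfect balance the figures lie between these and the unadjusted ones.

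**Step 4: which end of the range is plausible.** The Inclusion and exclusion criteria put a floor and a ceiling on the CES-D and HADS at entry (cut-offs of 16 and eight below, 39 and 15 above). Restricting the range of a baseline score generally lowers its correlation with the later score. The lower rows of r deserve more weight than the upper ones.

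**The case against.** The strongest reply is that silence is not exclusion. The section specifies multiple regression and provides for covariates. Nothing rules out the baseline score or the randomisation factors, and a journal article commonly leaves the full covariate list to the analysis plan. This stands against any claim that the model leaves these variables out. It does not dispose of the point, because the article does state a model, with a single named predictor and adjustment as an option on a confounding rationale. Fixing the adjustment is a better method, not just added detail.

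Three stronger readings are tempting, and the document does not support them.

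- A reader might infer that the trial falls short of its power. It does not: the 100 per condition is unadjusted, so what is forgone is a gain above plan.
- A reader might infer that covariates will be picked after the data are seen. The text does not say when or how they are chosen. It leaves room for this but does not state it.
- A reader might infer that "the treatment dummy as predictor" means one indicator for five arms, which would be a modelling error. The sentence is visibly garbled and the singular is probably shorthand. One indicator is also correct for a single pairwise contrast.

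It is also fair to say that ignoring the randomisation factors does not raise the false-positive rate, and that the size of any gain depends on a correlation the document does not give.

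**Conclusion.** The point holds as an improvement that costs nothing, not as an error that endangers the trial. The stated model commits to neither the baseline value of the outcome nor the factors used in allocation. Run that way, it would give less precise estimates and conservative standard errors. On the plan's own one-tailed basis, committing to baseline adjustment would raise power from about 0.79 to about 0.83, 0.89 or 0.96 for r of 0.3, 0.5 or 0.7, with the lower end more likely given the entry limits. These figures assume complete data, a linear relation between baseline and outcome, and the planned effect size. The randomisation factors should not be credited with a separate large gain, because two of the three are themselves depression and anxiety scores and overlap with the baseline values.

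**What to change.** Replace the two sentences on predictors and confounders with a stated primary model. Outcome score is regressed on:

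- arm indicators (four for a model with all five arms, or one for each pairwise contrast);
- the baseline value of the same scale, as a continuous covariate;
- the depression, anxiety and medication factors as they were used in the randomisation.

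Enter each baseline scale only once: where the outcome's own baseline scale is also a randomisation factor, it should not appear twice. State in the Randomization section which scales, and which categories if any, define the depression and anxiety factors, so that the model can match them. Drop the reference to possible confounders, and limit any other covariates to sensitivity analyses.

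The cost is a sentence or two of text. All the variables are already collected before randomisation, and the sample size need not change.

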#### Economic analyses

Economic costs of the intervention (internet application, costs of the coaches) will be calculated per participant, and both in money and hours working time. We will also conduct a true economic evaluation. The pertinent cost-data will be collected in the experimental and control conditions at baseline and at follow-up with help of the TIC-P [41]. The incremental cost-effectiveness ratio (ICER) will be calculated. Its uncertainty will be graphically represented in the ICER planed with help of the bootstrap method (with 2,500 bootstrap replications). Finally, the ICER acceptability curve will be plotted for several ceilings in the willingness to pay for a Quality-Adjusted Life Year (QALY) gained. Sensitivity analyses will be carried out to ascertain the robustness of the findings under different scenarios, e.g. under varying values of key-variables.

